## Abstract

**Background:**

Emergency abdominal surgery carries a 15% to 20% short-term mortality rate. Postoperative medical complications are strongly associated with increased mortality. Recent research suggests that timely recognition and effective management of complications may reduce mortality. The aim of the present trial is to evaluate the effect of postoperative intermediate care following emergency major abdominal surgery in high-risk patients.

**Methods and design:**

The InCare trial is a randomised, parallel-group, non-blinded clinical trial with 1:1 allocation. Patients undergoing emergency laparotomy or laparoscopic surgery with a perioperative Acute Physiology and Chronic Health Evaluation II score of 10 or above, who are ready to be transferred to the surgical ward within 24 h of surgery are allocated to either intermediate care for 48 h, or surgical ward care. The primary outcome measure is all-cause 30-day mortality. We aim to enrol 400 patients in seven Danish hospitals. The sample size allows us to detect or refute a 34% relative risk reduction of mortality with 80% power.

**Discussion:**

This trial evaluates the benefits and possible harm of intermediate care. The results may potentially influence the survival of many high-risk surgical patients. As a pioneer trial in the area, it will provide important data on the feasibility of future large-scale randomised clinical trials evaluating different levels of postoperative care.

**Trial registration:**

Clinicaltrials.gov identifier: NCT01209663

## Background

Worldwide an estimated 234 million surgical procedures are performed every year [1]. Overall, non-cardiac surgery carries low postoperative mortality rates of 1.4% to 1.9% [2-4]. However, this conceals the fact that a subgroup has a high risk of postoperative death. This high-risk group comprises patients often of advanced age with significant co-existent disease undergoing complex emergency surgery [4]. Emergency abdominal surgery carries a 15% to 20% short-term mortality rate [5-8], with cardiopulmonary complications and sepsis as the most frequent causes of death [9]. Postoperative medical complications are more important determinants of postoperative death than preoperative demographic characteristics, and intraoperative adverse events [8,10]. Recent research suggests that timely recognition, and effective management, of postoperative complications may reduce mortality [11]. Thus, early routine postoperative admission of high-risk non-cardiac surgical patients to intensive or intermediate care units could prove important. However, many countries have limited access to these facilities [4,12]. The majority of high-risk non-cardiac surgical patients are consequently treated on standard surgical wards with restricted resources for monitoring, and advanced treatment methods [4,13]. Intermediate care (IC) could be an appropriate level of care for stable postoperative patients with an *a priori* high risk of complications and death. IC is generally defined as a level of care intermediate between that provided by a general ward and an intensive care unit. An IC unit monitors and supports patients with, or likely to develop, acute (or acute on chronic) single organ failure [14-16]. The effect of postoperative IC compared to ward care on high-risk surgical patients’ outcome is only sparsely evaluated, and never in a randomised clinical trial [17-23] (Additional file 1: Search string).

The aim of the InCare trial is to evaluate the effect of postoperative IC following emergency major abdominal surgery in high-risk patients identified by an Acute Physiology and Chronic Health Evaluation (APACHE) II score of 10 or above. The APACHE II score is a well-established classification system of the severity of diseases used in intensive care units worldwide [24], which can be used on emergency major abdominal surgical patients as well [5,25-31]. Emergency major abdominal surgical patients with an APACHE II score of 10 to 11 and above have a 28% to 45% mortality rate compared to patients with an APACHE II score below 9 and 10 who evidence a mortality rate of 0% to 7% [27-31]. We hypothesise that postoperative IC will lead to a reduction in postoperative mortality by avoidance of, or timely recognition and effective management of, postoperative complications. Furthermore, we hypothesise that early admission to postoperative IC may reduce later admission to intensive care.

## Methods and design

### Trial design

The InCare trial is an ongoing multicentre, randomised, parallel-group, non-blinded clinical trial with 1:1 allocation. Emergency abdominal surgical patients are postoperatively allocated to either: (1) IC for 48 h; or (2) surgical ward care (standard treatment). The trial was initiated in October 2010, and we aim to enrol 400 patients.

### Setting

In Denmark all emergency surgical patients are treated in tax-financed public-healthcare centres. The total intensive and intermediate care availability in Denmark is 8.3 beds per 100,000 citizens in 2010, with seven intensive care beds per 100,000 citizens and 1.3 intermediate care beds per 100,000 citizens (unpublished data from The Danish Regions central office). In comparison the intensive care availability in the United States was 20.0 per 100,000 citizens, and in the United Kingdom it was 3.5 per 100,000 citizens in 2005 [32]. Currently seven Danish tertiary referral university affiliated public-healthcare centres are participating in the trial.

### Inclusion criteria

Patients are eligible for inclusion if: (1) they have undergone emergency gastrointestinal laparotomy or laparoscopic surgery; (2) they are ready to be transferred to the ward after a postoperative stay in a post-anaesthesia care unit or an intermediate/intensive care unit for <24 h; and (3) they have a perioperative APACHE II score of ≥10. We define emergency surgery as indicated surgery, which should be undertaken within 24 h.

Because of slower enrolment rate than anticipated, the steering committee have decided to include patients with Apache II scores of 10 and 11 although the original inclusion criteria was an Apache II score ≥12. This was initiated on 23 May 2012 after 192 enrolled patients. Patients with Apache II scores of 10 and 11 also have a high 30-day mortality and the potential to benefit from the IC intervention [27-31].

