### Randomisation

The patients are randomised using a telephone-based central interactive-voice-response system managed by the Copenhagen Trial Unit (CTU). The randomisation system is accessible around the clock. It ensures immediate computer-based allocation, and adequate allocation concealment. A computer-generated block randomisation, with the investigators unknown and varying block size is used. Stratification variables are: trial site; APACHE II score (10 to 14 or ≥15); and perforated viscera (yes *versus* no).

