### Sample size

Emergency major abdominal surgical patients with an APACHE II score ≥10/11 have a 28% to 45% mortality rate [27-31]. We assume that patients with an APACHE II score of ≥10 have a 30-day mortality of 38%. We aim to confirm or reject an intervention effect of 13% absolute risk reduction in mortality (a relative risk reduction of 34%), in accordance with the difference between group mortality detected in our recent observational study of optimised perioperative care in perforated peptic ulcer patients [48]. The sample size with a type 1 error risk of 5%, and a type 2 error risk of 20% (80% power), was estimated to 200 patients in each group [49].

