## Discussion

### Trial rationale

#### Participants

Our recent findings in emergency surgical patients with perforated ulcer [48] suggested that we should investigate the effects of IC in emergency major abdominal surgical patients with an APACHE II score ≥10. The APACHE II index is well-known to anaesthetists responsible for patient enrolment, and it reflects the presence of perioperative sepsis, cardiovascular and respiratory failure.

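### The APACHE II entry threshold fell from 12 to 10 after 192 of 400 patients, but the adjusted models still use one level for scores 10 to 14, and the 38% planning rate takes no account of the first phase

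*Protocol article*

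**What the plan says.** Under Inclusion criteria, the protocol article says the steering committee decided to "include patients with Apache II scores of 10 and 11 although the original inclusion criteria was an Apache II score ≥12". The timing is given: "This was initiated on 23 May 2012 after 192 enrolled patients". The reason is also given: "Because of slower enrolment rate than anticipated, the steering committee have decided". In support it adds "Patients with Apache II scores of 10 and 11 also have a high 30-day mortality and the potential to benefit from the IC intervention", citing references 27 to 31.

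The article gives figures from the same references in two places. Background reports 28% to 45% mortality for patients at or above a cut-off of 10 to 11, "compared to patients with an APACHE II score below 9 and 10 who evidence a mortality rate of 0% to 7"%. Sample size repeats the upper group: "Emergency major abdominal surgical patients with an APACHE II score ≥10/11 have a 28% to 45% mortality rate". It then assumes 30-day mortality of 38% for scores of 10 and above, an absolute reduction of 13 points, and 200 patients per group.

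Randomisation lists the stratification variables as "trial site; APACHE II score (10 to 14 or ≥15); and perforated viscera (yes *versus* no"). Statistical analysis uses the same two APACHE II levels as a covariate in the adjusted logistic model for 30-day mortality and in the adjusted Cox model for survival. Recruitment, screening and enrolment says the score is calculated electronically on the trial website.

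**The concern.** The population that can enter the trial changed about halfway through, but the analysis categories as stated do not show the change. Scores 10 and 11 sit in the same covariate level as 12 to 14. If mortality rises with the score, as the article's own contrast between 28% to 45% and 0% to 7% suggests, that level pools patients of different risk. The adjusted models then lose prognostic information that the trial already holds.

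Two further points follow. The article supports a statement about two particular scores with a figure that averages over every score above a cut-off. And one planning rate, assigned to scores of 10 and above, is applied to 400 patients of whom the first 192 had to score at least 12. What is at stake is some precision in the adjusted estimates, the clarity of the planning assumption, and a reader's ability to see the result for the population the trial began with.

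**Working it through.** **1. The plan's own figure.** Inputs from Sample size and Statistical analysis: 38% versus 38 − 13 = 25%, two-sided 5%, 80% power. The pooled-variance formula for two proportions, without continuity correction, gives 200 per group. Power at 200 per group is 80.1%. The stated size is reproduced exactly, so there is no arithmetic error.

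**2. Who is in the lower level.** Old criterion: at least 12. Lower level as now written: 10 to 14. For the first 192 patients it can hold only 12 to 14; for the remaining 400 − 192 = 208 it can hold 10 to 14. The article does not state how the lower stratum was labelled before the change, so 12 to 14 is inferred from the old criterion.

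**3. What the mortality figures cover.** The 28% to 45% covers everyone at or above the cut-off; the 0% to 7% covers those below it. Neither isolates scores 10 and 11. An average over scores of 10 and above does not fix the rate at its lowest end. For example, if 20% of such patients scored 10 or 11 with 10% mortality, an overall 38% needs only (0.38 − 0.20 × 0.10)/0.80 = 45% at 12 and above.

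**4. Effect on power.** Two inputs are missing from the article and are assumed: the share s of the 208 who score 10 or 11 (20% to 40%, so k = 208s, about 42 to 83 patients), and their control mortality q (7% to 28%, the top of the lower group's range and the bottom of the upper group's). The risk ratio is held at 25/38, with 200 per group.

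*Reading A: 38% belongs to scores of 12 and above.* Pooled control rate = [(400 − k) × 0.38 + k × q]/400.

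*Reading B: 38% belongs to scores of 10 and above, as Sample size says.* Rate at 12 and above = (0.38 − s × q)/(1 − s). Pooled control rate = [192 × that rate + 208 × 0.38]/400.

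| s | q | A: control rate | A: power | B: rate at ≥12 | B: control rate | B: power |
|---|---|---|---|---|---|---|
| 20% | 7% | 34.8% | 74.9% | 45.8% | 41.7% | 85.4% |
| 20% | 28% | 37.0% | 78.5% | 40.5% | 39.2% | 81.9% |
| 40% | 7% | 31.6% | 69.1% | 58.7% | 47.9% | 92.1% |
| 40% | 28% | 35.9% | 76.9% | 44.7% | 41.2% | 84.7% |

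Reading A gives about 69% to 79%; reading B gives about 82% to 92%. They lie on opposite sides of the planned 80%.

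**5. An analysis restricted to scores of 12 and above.** Patients per group = (400 − k)/2, about 179 at s = 20% and 158 at s = 40%. At 38% versus 25%, power is about 76% and 70%.

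**The case against.** The strongest reply is that nothing is concealed and nothing is biased. Inclusion criteria gives the old threshold, the new one, the date, the count and the reason. Patients before and after the change were randomised concurrently 1:1, so a coarse covariate cannot bias the comparison. Adjusting for the factors used in stratification is standard practice, and the unadjusted logistic model does not depend on this coding at all. All of this stands.

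Several stronger readings are tempting, and the article does not support them.

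- A reader might infer that the added patients are low-risk. The 0% to 7% belongs to a group that remains excluded, and the mortality at 10 and 11 is simply not shown.
- A reader might infer that references 27 to 31 contain no rate for those scores. They are not available here; one can say only that the article does not reproduce such a rate.
- A reader might infer that the change cost the trial power. That holds only if 38% is moved to scores of 12 and above. Sample size assigns it to 10 and above, and on that reading power rises.
- A reader might infer that a null result could not be told apart from dilution. Control mortality and the scores will both be observed.
- A reader might take the Discussion sentence under Participants, that earlier findings "suggested that we should investigate the effects of IC in emergency major abdominal surgical patients with an APACHE II score ≥10", as rewriting history. It describes the current criterion, and the change is disclosed elsewhere.

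A supportive analysis by entry threshold may also exist in an analysis plan that is not shown, so its absence from the article is not an error. What the reply does not answer is the covariate coding, which the article states and which uses less of the score than the trial holds.

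**Conclusion.** The point holds in a limited form. The adjusted models assign one risk to scores 10 to 14, although the make-up of that level could change after patient 192 and a finer covariate is already available. The article shows no mortality figure specific to scores 10 and 11. The single 38% is labelled for scores of 10 and above, yet about half the trial (192/400 = 48%) entered under a criterion of at least 12.

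The consequence is some avoidable loss of prognostic information and an unclear planning assumption. The size of the loss in precision cannot be computed from the article. The power figures above are a sensitivity range, because the share of patients at 10 and 11 and their mortality are both assumed; across the two readings even the direction is open. The stated sample size is arithmetically correct and the randomised comparison is sound. This is an improvement to consider and does not threaten the trial's validity.

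**What to change.** Before data release:

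1. In Statistical analysis, enter APACHE II in the adjusted logistic and Cox models as the recorded score, or as three bands (10 to 11, 12 to 14, at least 15). Leave the randomisation strata unchanged.
2. Name one supportive analysis of 30-day mortality in patients scoring at least 12, and state that its power is lower, about 70% to 76% at 38% versus 25% under the shares assumed above. It describes the population the trial began with; it would not settle a null result.
3. In Sample size, note that 38% is an assumption for scores of 10 and above, and that the first 192 patients were enrolled at 12 and above.

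The cost is a few sentences and one extra model. No new data are needed, since the score is already calculated electronically. With 199 patients enrolled at 1 June 2012 (Trial status), there was still time to specify this in advance.

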### Exclusion criteria

Exclusion criteria are as follows: (1) appendectomy; (2) laparoscopic cholecystectomy; (3) negative diagnostic laparoscopy; (4) intensive care not indicated (patients on palliative care, or with irreversible organ failure); (5) previous participation in the trial; (6) age <18 years; (7) trauma; and (8) no IC bed available.

### Recruitment, screening and enrolment

We recruit patients postoperatively in the post-anaesthesia care unit and intensive/intermediate care unit. All adult patients who have undergone the relevant surgical procedures have a venous and arterial blood gas sample taken upon arrival from the operating theatre. Uniformity of trial site standard postoperative vital-sign monitoring is ensured, enabling calculation of the APACHE II score, when patients are ready to be transferred to the surgical ward in accordance with the trial site’s discharge criteria - local adjusted versions of the Danish national recommendations [33] (Additional file 2: National discharge recommendations). At this point of time the attending anaesthetist screens for trial eligibility using a standard screening form with flowcharts (Figure 1). If none of the exclusion criteria 1 to 7 apply, the APACHE II score is calculated from the worst parameter values measured 12 h preoperatively, peroperatively, and up to 12 h postoperatively. If there is missing data for the APACHE II score calculation, when the patient is transferable to the ward, current values are used. GCS score, blood pressure and heart rate recorded during anaesthesia are not included in the APACHE II score calculation. The APACHE II score is calculated electronically on the InCare trial website [34]. If the patient has an APACHE II score of ≥10 the anaesthetist checks that an IC bed can be established at the intermediate care, intensive care or post-anaesthesia care unit. If an IC bed is not available, the patient is registered as ‘not included due to lack of IC bed’ and transferred to the ward. If an IC bed is available, written consent is obtained from the patient or a legal representative, if the patient is incapable. If it is not possible to contact a legal representative within 2 h, the patient is included in the trial, and written consent is obtained as soon as possible.

**Figure 1 F1:**
[figure not shown]
Screening flowchart.

### Randomisation

The patients are randomised using a telephone-based central interactive-voice-response system managed by the Copenhagen Trial Unit (CTU). The randomisation system is accessible around the clock. It ensures immediate computer-based allocation, and adequate allocation concealment. A computer-generated block randomisation, with the investigators unknown and varying block size is used. Stratification variables are: trial site; APACHE II score (10 to 14 or ≥15); and perforated viscera (yes *versus* no).

### Interventions

#### Intermediate care

IC is initiated as soon as the patient is allocated, and continues for at least 48 h. The IC bed is situated at an intermediate care, an intensive care or a post-anaesthesia care unit, which can provide the outlined intervention (Table 1). IC is defined as a minimal monitoring level and maximal treatment level. The minimal monitoring level is applied when the patient’s vital signs are stable. If the patient deteriorates, the level of monitoring and treatment is increased as indicated. When the maximal level of treatment defined in the IC is exceeded, that is when there is a need for invasive ventilation, emergency dialysis, parallel sympathomimetic drug infusion or invasive arterial-blood pressure monitoring, the patient is categorised as an intensive care patient. However, the patient remains in the trial for observation of the outcome measures. Surgeons and intensivists make compulsory protocol-based rounds on a daily basis using a standard form (Additional file 3: Surgeon - protocol-based round and Additional file 4: Intensivist - protocol-based round). All medical treatment and investigations are made on medical indication alone, not determined by the trial-protocol. Forty-eight hours after randomisation, or at morning handover if the patient is included at night, re-evaluation is made. If patients are stable, and local discharge criteria are met, they can be transferred to the surgical ward.

**Table 1 T1:** Definition of intermediate care

**Observation**	**Minimal monitoring level^a^**	**Treatments goals^b^**	**Comments**
Level of consciousness	Every 8 h	GCS: 15	
Respiratory rate	Every second hour	RR: 10 to 20	If the patient has stable vital signs the RR is not measured during nights
Oxygenation	Continuous pulse oximetry	SpO_2_ ≥94%	Continuous pulse oximetry when the patient is supine or sitting in a chair. Discontinued during mobilisation
Blood pressure	Every second hour	MAP: 65 to 110 mmHg	If the patient has stable vital signs the MAP is not measured during nights
Heart rate	Continuous ECG monitoring	HR: 50 to 100	Continuous ECG when the patient is supine or sitting in chair. Discontinued during mobilisation. Diagnostic ECG on indication. If arrhythmia or ischaemia is detected the treatment goals are adjusted to current recommendations
		No ischemia	
Diuresis	Every hour	≥0.5 mL/kg/h	During mobilisation the diuresis is summed every third hour
Temperature	Every 8 h	36°C to 38°C	
Pain Visual Assessment Score	Every 8 h	VAS: 0 to 2 during rest	No VAS scoring during sleep
		Epidural: Able to move both legs	
Central venous pressure	Every 8 h	8 to 12 mmHg	CVP and S _c_VO_2_ is only registered if there is a central venous catheter in place. The central venous catheter is removed when possible
Central venous oxygen saturation	Every 8 h	SpO_2_ ≥ 70%	
Standard blood samples	Every 24 h	Within normal reference values	Hgb ≥4.5 mmol/L
			Hgb ≥6.0 during sepsis or heart disease
**Treatment****(if needed)**	**Maximal treatment level**	**Treatments goals**	**Comments**
Single sympathomimetic drug support	Continuously	MAP: ≥65 mmHg	
		Diuresis: ≥0.5 mL/kg/h	
Oxygen therapy on open systems	Continuously	SpO_2_ ≥94%	Unless contraindicated, oxygen therapy is discontinued when oxygenation is ≥94% without oxygen therapy. During nights: minimum 2 L supplemental oxygen is given
Positive Expiratory Pressure (PEP) therapy	Assistance to PEP therapy: once per hour	SpO_2_ ≥94%	If the patient does not need assistance with PEP therapy, guidance in self-administration of PEP therapy must be available
Non-invasive ventilation	Continuously	Normocapnia and normoxic	
Volume / Fluid therapy	Continuously	MAP: ≥65 mmHg	Fluid balance: Evaluation frequency in accordance with monitoring level and vital signs
		Diuresis: ≥0.5 mL/kg/h	
		S _c_VO_2_ ≥70%	
		CVP: 8 to 12 mmHg	

During evening and night shifts: Staff specialist in anaesthetist/intensive care medicine on in-house duty and staff specialist in surgery on call.

^a^The minimal monitoring level is exceeded when necessary (for example, deterioration).

^b^All treatment goals are adjusted to the individual patient’s co-morbidities, physiological status and in the event of complications in agreement with current recommendations (for example, troponin T/I is measured when cardiac ischaemia is suspected).

